## Introduction

Befriending services are often used to provide social connection to individuals who are socially isolated. The service typically involves trained volunteers being matched with a service user in a structured manner, e.g. for weekly visits. Befriending services may improve health, since elective relationships have a positive impact on health (
Golden *et al.*, 2009). Befriending services have also been shown to reduce loneliness (
Lawlor *et al.*, 2014). Befriending may also benefit brain health, since social relationships are associated with a reduced risk of developing dementia (
Kuiper *et al.*, 2015;
Morley *et al.*, 2015). A relatively new term, brain health refers to the preservation of optimal mental and cognitive function in the face of age-related decline, and in the absence of disease-related decline (
Wang *et al.*, 2020). 

However, the theoretical basis for how befriending might impact health is poorly understood (
Lester *et al.*, 2012). The causal cascade model has been used to explain the impact of social engagement on health (
Berkman *et al.*, 2000) and cognitive decline (
Zunzunegui *et al.*, 2003) and could constitute a model of the relationship between befriending and brain health. In this model, social engagement confers a health benefit to individuals at a series of levels from the macro (cultural norms, urbanisation), the mezzo (social network size, reciprocity of ties) to the micro (emotional social support, intimate contact), which all influence health or cognitive functioning via behavioural (e.g. help-seeking behaviour, diet), psychological (e.g. self-esteem), and physiological (e.g. immune system function, allostatic load) pathways.

Befriending may improve health partly via its effect on loneliness (
McGoldrick *et al.*, 2017), which affects 10% of older Irish adults (
Harvey & Walsh, 2016). Reducing loneliness is a desirable outcome because of its associations with various undesirable outcomes including depression (
O'Luanaigh & Lawlor, 2008), dementia (
Wilson *et al.*, 2007) and poor quality of life (
Ekwall *et al.*, 2005). Researchers have predicted that befriending services could reduce dementia by 0.21% through reducing loneliness (
Owen *et al.*, 2016). However, this prediction has not been formally evaluated.

As has been highlighted previously (

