### Aims and objectives

**Overall study aim:** To improve understanding of the health-related impacts of befriending on older adults, and to understand the role of loneliness in this regard.

**Hypothesis 1:** Befriending services have a positive impact on health-related quality of life and brain health.

**Hypothesis 2:** Receipt of a befriending service moderates the negative impact of loneliness on health-related quality of life and brain health.

**Objective of qualitative component:** To explore potential mechanisms by which befriending impacts health in a series of dyadic and individual semi-structured interviews with recipients of a befriending service and their partnered befrienders.

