Living in the greater Dublin area.Participants must have contacted ALONE with an interest in receiving befriending services, and must be on a waiting list to receive such services at the time of their trial registration.Participants must be aged 60 and over.Participants must have the ability to provide informed consent.Participants must self-report that they experience loneliness “at least sometimes”.

Exclusion criteria for quantitative component:
Participants must not self-report receipt of a diagnosis from a medical doctor of any of the following: intellectual disability including autism spectrum disorder or psychotic disorder, dementia, serious memory impairmentParticipants must not live further than an hour’s drive from Dublin.

Inclusion criteria for qualitative component:
Participants to be recruited in pairs must have been paired as befriender-befriendee for at least six months, and the befriendee must have been in receipt of any befriending from the service for a minimum of one year.Living in the greater Dublin area.Befriendees must be aged 60 or over.Both pair members must have the ability to provide informed consent.Both pair members must have sufficient language ability to engage in the interview.

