** Loneliness is measured using the modified five item University of California Los Angeles (UCLA) loneliness scale (
Russell, 1996) at each of 13 observations made two weeks apart for a minimum of two observations before the intervention begins and a maximum of 11 observations after. In this scale, five items ask participants to rate how frequently they experience each aspect of loneliness, and scores are summed to yield a range of 0-10 (with higher scores indicating more loneliness). The scale is well-validated with high internal consistency (alpha = 0.89) and test-retest reliability (r = 0.73 over two months), and has been used in cohort studies of ageing internationally including the Irish Longitudinal Study on Ageing (
Kenny *et al.*, 2010).

**
*Time-varying covariate: Change in social isolation.*
** The revised Lubben Social Network Scale is a short (six item) and well-validated scale to measure social isolation in older adults (
Lubben & Gironda, 2004). Six questions probe the level of received support from family and friends. Responses are equally weighted and give scores of 0-30 with higher scores indicating more perceived social support/less isolation.

For all above outcomes, change over time is the analysis metric. All outcomes are measured a maximum of 13 times from which trends can be created. Trends will be treated as random effects to account for inter-individual variation and intra-individual variation. All outcomes were chosen with clinical relevance in mind. Befriending services are typically provided because of loneliness so it is crucial to explore whether loneliness typically reduces as a result of uptake in the service. Health-related quality of life and brain health are two of the most critical outcomes for older adults.

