### Analytic plan

In order to test hypothesis 1, that befriending services will lead to a positive change in health-related quality of life and brain health, two separate generalised additive models will be performed. Data are longitudinal, with 13 time points at which they are collected, before and after a befriending match has been made. The data analysis protocol for the quantitative component of the study is as follows: first, after data collection and audit, visual inspection of plotted data at the individual and group level will be done for both outcomes of interest. Next, pre-intervention and post-intervention trends will be inspected, as well as mean shifts, slope changes, and variability across participants. With respect to verbal fluency as an outcome, data will be analysed for practice effects using published guidelines (
Vivot *et al.*, 2016) and if practice effects are detected, this should be specified in the final model. The modelling of these practice effects is itself of interest and can inform future research attempting to conduct repeated cognitive measures. If practice effects are considerable, this could represent a risk for the interpretability of the results, but since the cognitive outcome is a secondary measure in the study design, this risk does not affect the overall study feasibility. Inferential analyses will be conducted using a generalised additive model (GAM) (
Shadish *et al.*, 2014b) based on a multilevel approach where time points are nested within participants (
Shadish *et al.*, 2014b). This approach is semi-parametric, and calculates autocorrelations from extracted residuals. Time will be scaled such that point 0 is the end of the baseline (two time points of data collection will be conducted during baseline). The GAM approach improves on some key limitations of the multilevel approach, since with the latter, the functional form of the trend must be known, whereas in the former, a smoothing function can be used to model the trend in the data. The moderation effect (investigating whether befriending moderates the impact of loneliness on health and cognitive function) is modelled as an interaction term: the product of the two predictors (loneliness and befriending phase, operationalised as 0 indicating pre-intervention, and 1 indicating post-intervention). This modelling approach will be deployed using the mgcv package in R Studio software (
Wood, 2011).

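### If loneliness falls between phases and its effect is curved, the Hypothesis 2 product term can show the curve as moderation; specify a smooth main effect for loneliness

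*Protocol article*

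**What the plan says.** Hypothesis 2 (Aims and objectives) reads: "Receipt of a befriending service moderates the negative impact of loneliness on health-related quality of life and brain health". The Analytic plan tests it with an interaction term, "the product of the two predictors (loneliness and befriending phase, operationalised as 0 indicating pre-intervention, and 1 indicating post-intervention". The same section prefers a generalised additive model (GAM) in mgcv to a parametric multilevel model because "a smoothing function can be used to model the trend in the data". That sentence concerns the trend over time. The section does not say whether the main effect of loneliness is a straight line or a smooth. The planned inspections cover trends, mean shifts, slope changes and variability, but not the shape of the relation between loneliness and the outcome.

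On whether loneliness moves between phases:
- The Introduction says "Befriending services have also been shown to reduce loneliness" and reports the same from a study by members of the team.
- Outcomes says "it is crucial to explore whether loneliness typically reduces as a result of uptake in the service".
- Entry is selective: "Participants must self-report that they experience loneliness" at least sometimes (Sample selection and recruitment).

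Loneliness is measured at every observation ("scores are summed to yield a range of 0-10"), with "a minimum of two observations before the intervention begins and a maximum of 11 observations after".

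**The concern.** A product of loneliness and a 0/1 phase lets only the straight-line slope of loneliness differ by phase. If people sit lower on the loneliness scale in phase B, the two phases sample different stretches of the same curve. Where harm per point grows with loneliness, the phase B slope is flatter for that reason alone, and the product reports this as befriending softening the impact of loneliness. Where harm levels off at high loneliness, the sign reverses, so the product shows false worsening or masks real buffering. A fall from any cause is enough, including regression to the mean after selecting people who report loneliness.

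Moderation is the question in the study title. A significant product would not by itself separate moderation from an ordinary curved relation combined with a fall in loneliness. Outside readers may be unable to check later: the Analytic plan says participant-level data will not be archived and hopes to share a covariance matrix, and a covariance matrix of the listed variables does not reveal curvature.

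**Working it through.** **Inputs from the protocol (Sample; Outcomes).** EQ-5D SD 0.23, minimally important difference 0.074, intraclass correlation 0.5, autocorrelation 0.5, alpha 0.05 (sidedness not stated; two-sided used), 85 participants, 13 observations, at least 2 of them in phase A.

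**The plan's own figures.** The effect size is 0.074 / 0.23 = 0.322, which reproduces the stated 0.32. The 85 was calculated for the phase effect; the article gives no calculation for Hypothesis 2. Generalised least squares (GLS) with these inputs gives 20 to 43 rather than 85. The simulation macro that the protocol used was not available, so this does not show 85 to be wrong. I take 85 as given.

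**Assumptions not in the protocol.** Phase A loneliness mean 6, SD 2.2, 70% of variance between persons; falls of 0 to 3 points; a total EQ-5D difference of 0.15 or 0.30 across the 0-10 scale; the curve shapes; EQ-5D not capped at 1.

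**Step 1, algebra.** Suppose the mean outcome is -c x L², with no moderation. The local slope is -2cL. If mean loneliness drops by d, the slope in B minus the slope in A is -2c(L - d) + 2cL = 2cd. For a range of 0.30, c = 0.30 / 10² = 0.003. The false product is then:
- d = 1: 2 x 0.003 x 1 = 0.006 per point, or 0.06 over the full scale
- d = 2: 0.12 over the full scale
- d = 3: 0.18 over the full scale

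The average slope over the scale is -0.30 / 10 = -0.03 per point.

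**Step 2, simulation.** 600 runs per cell, 85 participants, 2 + 11 observations, no true moderation. The fit was GLS with free visit effects and covariance known up to scale. Rejection rate of the product with a straight-line main effect:

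| True shape (EQ-5D range) | No fall | 1 point | 2 points | 3 points |
|---|---|---|---|---|
| Convex (0.30) | 4% | 15% | 41% | 63% |
| Convex (0.15) | 5% | 7% | 12% | 20% |
| Concave (0.30) | 3% | 13% | 37% | 65% |
| Concave (0.15) | 5% | 9% | 14% | 24% |
| Threshold at score 5 (0.30) | 6% | 37% | 90% | 99% |
| Threshold at score 5 (0.15) | 6% | 14% | 34% | 61% |
| Linear (0.15 or 0.30) | 6% | not run | 5-6% | not run |

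Monte Carlo error near 5% is about 2 points either way. For convex 0.30 the mean false coefficient over the full scale was 0.056, 0.105 and 0.146, against 0.06, 0.12 and 0.18 from Step 1; clipping scores to 0-10 explains the shortfall. Convex and threshold shapes gave a positive sign (false buffering), concave shapes a negative one (false worsening).

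**Step 3, a second set-up.** 400 runs per cell, phase A mean 5.5, the same curve -0.003 x L². A 1.0-point fall gave a product of about +0.005 per point and 16% false positives; a 1.5-point fall gave about +0.007 and 24%. Over curvatures of 0.002 to 0.004 the rate was 9-45%. Curvature arising only from the EQ-5D ceiling at 1 gave 3-12%.

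**Step 4, curved main effect, same product.** In the Step 2 set-up, a quadratic or spline main effect gave 3-7% rejection in every scenario. Mean bias was about 0.005 or less with the spline, and at most 0.028 with the quadratic (threshold shape, 3-point fall). In the second set-up the quadratic gave 4-6%.

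**Step 5, cost.** The standard error of the product rose from 0.0057 to 0.0059-0.0062 (0.0059 / 0.0057 = 1.04; 0.0062 / 0.0057 = 1.09). Power for a true moderation of half the slope (0.15 on a range of 0.30, 1-point fall) went from 0.71 to 0.67.

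**The case against.** The strongest reply is that the defect is not in the text. A reader might infer that the plan fixes loneliness as linear and smooths time alone. It says neither. The model is a semi-parametric GAM, and a smooth main effect beside the stated product fits the wording and removes the problem. How a main effect enters is often left to a fuller plan, and this article condenses one that is not shown. This stands, and it is why the point is a recommended specification and not a demonstrated error.

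The inputs can also be challenged. The protocol gives no figure for the curve, for the size of any fall, or for the slope of EQ-5D on loneliness. A range of 0.30 is about four times the minimally important difference (0.30 / 0.074 = 4.1), and the 0.40 behind the 45% figure is about 1.7 SD (0.40 / 0.23). With the convex curve at 0.15, a 1-point fall gives 7%, within Monte Carlo error of nominal. The one source of curvature tied to the instrument, the EQ-5D ceiling, does little. This stands too: the inflation is conditional, and its size is unknown.

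A reader might also infer that the plan predicts a fall in loneliness. Outcomes speaks only of exploring whether it reduces. The Introduction cites earlier reductions without a size, so a fall is plausible but not assured.

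Finally, a product with a 0/1 phase is the conventional moderation test, and the caveat is general. That is true, but here the intervention is thought to shift the moderated predictor itself, and the remedy lies within the software already chosen.

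**Conclusion.** The point holds as a conditional risk with a cheap remedy. Bias needs three things together: a straight-line main effect (the natural reading, not stated), a shift in loneliness between phases (plausible from the Introduction and from selection at entry), and a curved relation (assumed). With all three, false positives for Hypothesis 2 ran from about 7% for a weak convex curve and a 1-point fall to 63% for a strong convex curve and a 3-point fall, and up to 99% for a strong threshold. Without a fall, or with a linear relation, the test keeps about 5%.

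Two stronger conclusions are not supported. One is that a significant product will be an artefact: in many of the assumed scenarios rejection is only modestly above nominal. The other is that the bias favours Hypothesis 2: that is so only if harm steepens with loneliness, and a flattening curve pushes the other way. The simulations concern EQ-5D. The same reasoning applies to verbal fluency, but its size was not computed.

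**What to change.** In the Hypothesis 2 models, state that loneliness enters as a smooth main effect in the same mgcv fit, or at least with an added quadratic term. Keep the loneliness-by-phase product as the moderation test. Report the distribution of loneliness scores in each phase and how far they overlap, and interpret moderation over the shared range.

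The cost is one model term and the small losses of precision and power shown in Step 5. The smooth is preferable to the quadratic because it left less bias under a threshold shape.

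Separate smooths of loneliness by phase should be a sensitivity analysis at most. Phase A may hold only two observations per person, and the cost of that option was not computed.

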### Oversight and monitoring

The trial is being conducted in only one centre so all coordination of trial activities is managed by the core research team at the host institution. Other project governance structures include a Project Management Board and a Project Steering Group. The Project Management Board is made up of the wider project team and meets once per quarter to review project progress and discuss plans for upcoming activities. A Project Steering Group is made up of client representatives from ALONE, representatives from the Befriending Networks Ireland (BNI) Advisory Panel and members of the wider project team. This Steering Group will meet on multiple occasions throughout the project to provide the research team with additional input and perspectives on the outcomes being studied; to ensure that the research topics, planned methodologies, language and format of study materials etc. are appropriate and acceptable; to assume the role of data monitoring; and to advise on and be involved with dissemination activities such as public workshops.

### Ethics

This study has received ethical approval from the Faculty of Health Sciences REC at Trinity College Dublin (Ethical Approval Reference Number: 180501). Any changes to the trial protocol that require an amendment to the existing ethical approval will be submitted in writing to the relevant REC at the host institution. Any proposed changes to the study protocol will be discussed and approved at a meeting of the Project Management Board. If any significant changes are made to the protocol that will impact on participants’ engagement with the study (e.g. changes to eligibility criteria or outcome measures), participants will be contacted to discuss these and a written description of these changes will be posted to participants where appropriate.

### Dissemination plans

Conference presentations and publications in peer-reviewed journals will be one method of dissemination. These will be done following the data analysis and prior to the process of application and translation of study results. Two publications (one describing quantitative outcomes in a health psychology journal, one describing mixed methods findings in a health and ageing journal), and two conference publications (one national - Irish Gerontological Society, and one international - Gerontological Society of America or EU Geriatric Medicine Society) will likely arise from the study with all collaborators (co-authors of this protocol) invited to participate in authorship following ICMJE guidelines on authorship criteria. Dissemination activities tailored to the needs of the knowledge user organisation will also be conducted, such as presenting the research at knowledge user events, and engaging in public relations exercises with personnel from the knowledge user organisation, to raise awareness of the research and of the available befriending services. Policy recommendations will be diffused across stakeholders, and disseminated to policymakers, and findings will finally be disseminated to community members in the form of a launch event with a lay report provided.

### Study status

Recruitment and data collection for both the quantitative and qualitative components of the study are ongoing. Recruitment to the quantitative component began in November 2018. To date a total of 49 participants have been recruited to the quantitative study. Recruitment to the qualitative component began in November 2019 and a total of seven befriender-befriendee dyads have completed qualitative interviews to date. It is anticipated that recruitment for both components will be completed by December 2020.

## Discussion

This protocol describes the pragmatic, embedded evaluation of an existing service which claims to reduce loneliness and mitigate the impact of loneliness on health outcomes for older adults. Currently we are recruiting during the COVID-19 pandemic in which, nationally, older adults are among those being advised to “cocoon” and remain in the home, potentially leading to increased risks of loneliness and social isolation, and higher country-level demands for services to resolve such issues. Inevitably, recruitment has slowed down because fewer services are available to older adults, but recruitment is beginning to recover (June 2020). All data collection and recruitment procedures are, for the time being, conducted by phone to avoid face-to-face visits yielding increased risk of COVID-19 transmission to older adults. Since our sample are at risk of social isolation, it is possible that the data collection process itself will constitute social engagement, and we will reflect on this during the data collection process. It is hoped that the completion of our study will add to the evidence base for the uptake of befriending services for older adults at risk of, or experiencing, loneliness and social isolation.

## Data availability

### Underlying data

No data are associated with this article.

### Extended data

Open Science Framework: HALO: Loneliness and Health: The moderating role of befriending services
https://doi.org/10.17605/OSF.IO/YKZTP (
[name] *et al.*, 2020)

This project contains the following extended data:
- HALO Consent Form_Qualitative Study.pdf- HALO Consent Form_Quantitative Study.pdf- HALO Participant Information Leaflet_Qualitative Study.pdf- HALO Participant Information Leaflet_Quantitative Study.pdf- HALO Qualitative Interview Schedule.docx

### Reporting guidelines

Open Science Framework: SPIRIT checklist for ‘HALO: Single-case experimental design study evaluating the moderating impact of a befriending intervention on the association between loneliness and health in older adults’.
https://doi.org/10.17605/OSF.IO/YKZTP (
[name] *et al.*, 2020)

Data are available under the terms of the
Creative Commons Zero “No rights reserved” data waiver (CCO 1.0 Public domain dedication).
